## Abstract

**Introduction:**

Target trial emulation is a framework for evaluating the effects of treatments using observational data. The trial emulation approach involves specifying key elements of a protocol for a target trial (a randomised controlled trial designed to address the question of interest) and then describing how best to emulate the trial using observational data. Recent years have seen an uptake of target trial emulation in several disease areas, although there are limited examples in cystic fibrosis (CF). This protocol describes a study which aims to assess the applicability of target trial emulation in CF. We aim to emulate an existing trial in CF and assess to what extent the results from the trial can be replicated using registry data.

**Methods and analysis:**

The target trial is a published randomised controlled trial which found evidence for beneficial effects of azithromycin use on lung function in young adults with CF. Two emulated trials are planned: one using data from the UK CF Registry and one using data from the US CF Registry. The inclusion and exclusion criteria, treatment and outcome definitions, follow-up period, and estimand of interest are all designed to match the published trial as closely as possible. The analysis step of the trial emulations will use causal inference methods to control for confounding. Results obtained in the emulated trials using registry data will be compared with those from the target trial.

**Ethics and dissemination:**

Ethical approval has been granted by the London School of Hygiene and Tropical Medicine Ethics Committee (Ref: 29609). This study has also been approved by the UK CF Registry Research Committee and the North Star Review Board. The results of this study will be published in a peer-reviewed journal and presented at relevant scientific conferences.

STRENGTHS AND LIMITATIONS OF THIS STUDYWe use data from the UK and US Cystic Fibrosis (CF) Registries. These are the two largest national CF registries, and the UK CF Registry is cited as an exemplar patient registry in the National Institute for Health and Care Excellence real-world evidence framework.We use the target trial emulation approach. This approach helps to clearly articulate the study design and to avoid certain biases. We provide an example of target trial emulation in a disease area where there are limited applications of this approach for estimating treatment effects.The CF registries do not contain data on treatment doses or adherence, which limits our ability to match the treatment strategies in the target trial precisely.The CF registries do not contain data for all secondary outcomes used in the target trial.

## Rationale and background

 Randomised controlled trials (RCTs) are the gold-standard approach for evaluating the effects of treatments. However, RCTs are costly, and sufficiently large trials are not always feasible, particularly in patient populations with a rare disease, such as cystic fibrosis (CF). When an RCT is not feasible, an alternative is to use observational data to ‘emulate’ a trial.^1^ The trial emulation approach involves specifying key elements of a protocol for a target trial (an RCT we would like to conduct, if it were feasible) and then describing how best to emulate the target trial using the observational data at hand. This approach combines the study design principles of RCTs with an analysis appropriate for observational data.

Recent years have seen an uptake of target trial emulation in several disease areas.^2^,^7^ There is also rising interest in emulating existing RCTs in an attempt to replicate the results from the existing RCTs using observational data. The RCT DUPLICATE initiative recently published the results of 32 trial emulations using insurance claims data to replicate existing trials.^8^ They found that emulated trials based on insurance claims data can obtain similar results to the original RCTs. Matthews *et al*^9^ used Swedish registry data to emulate the Thrombus Aspiration in ST-Elevation Myocardial Infarction in Scandinavia randomised trial.^10^ Admon *et al*^11^ used target trial emulation to predict results of the Preventing Hypoxaemia with Manual Ventilation during Endotracheal Intubation Trial^12^ before they were published.

Despite the widespread use of target trial emulation across other areas of medicine, there are limited applications within the CF literature^13 14^; thus, its applicability to CF remains unclear. We aim to assess the applicability of target trial emulation in CF using data from the UK and US CF patient registries by emulating a published RCT within CF and assessing the extent to which the RCT findings could be replicated. Here, we set out the trial emulation protocol, including the statistical analysis plan. We follow the reporting guidelines recommended in the HARmonised Protocol Template to Enhance Reproducibility.^15^

## Research question and objectives

The primary objective is to emulate a published RCT of the effects of azithromycin in young adults with CF by Clement *et al*^16^ using observational data from two patient registries and to assess the extent to which the RCT results can be replicated. The RCT of Clement *et al*^16^ provides the target trial that this study aims to emulate. This trial was selected as we anticipate that it will be possible to replicate using the UK and US CF Registry data, based on our knowledge of the treatment and outcome data recorded. Table 1 summarises the research question addressed in the target trial.

**Table 1 T1:** Description of the primary research question addressed in the target trial (Clement *et al*^16^)

Objective:	Investigate whether long-term use of azithromycin is associated with respiratory benefits in young people with CF
Population:	CF patients aged older than 6 years and forced expiratory volume in 1 s (FEV_1_%) of 40% or more.
Exposure:	Oral azithromycin
Comparator:	Placebo pills
Primary outcome:	Change in FEV_1_%
Time:	12 months
Setting:	Patients recruited from 18 CF accredited care centres in France
Main measure of effect:	Difference in change in FEV_1_% from baseline between treatment groups

CFcystic fibrosis

## Data sources

### UK CF registry

The UK CF Registry was established in 1995 and is a national database sponsored and managed by the CF Trust, with UK National Health Service research ethics approval. It records longitudinal data on approximately 99% of people with CF in the UK.^17 18^

Data are collected on time-invariant variables, such as sex at birth, cystic fibrosis transmembrane conductance regulator (*CFTR*) genotype, date of birth, diagnosis data and longitudinal variables that change over time. Longitudinal data are collected at approximately annual review clinic visits on over 250 variables covering several domains. These include clinical measurements taken on the day, and other variables covering the previous 12 months period such as: hospital admissions, treatments prescribed, culture and microbiology, health complications, nutrition, physiotherapy, smoking and outcomes (death and transplants). In 2016, the UK CF Registry started collecting treatment prescription start and stop dates.

### US CF registry

The US CF Registry began collecting data on people with CF in the USA in 1986 and is managed by the CF Foundation. It contains longitudinal information on approximately 80% of people with CF in the USA.^19^,^21^

Data are collected on demographic characteristics and on longitudinal variables that change over time. Data collection takes place at ‘encounter visits’ at CF care centres, with data also being abstracted annually. This study will use the encounter visit data which includes relevant information regarding hospitalisations, clinical measurements, medication usage, culture and microbiology, health complications. The encounter visits include routine clinical visits and visits in a hospital or the individual’s home. The non-routine hospital and home intravenous visits may be due to an individual experiencing worsening of their respiratory symptoms, and therefore, their lung function may be unstable at this time. These are referred to as ‘unstable’ visits, whereas routine clinical visits are referred to as ‘stable’ visits. The analyses in this study will use data from the stable visits only.

## Research methods

### Study design

We will conduct two studies nested within existing longitudinal data sets (one using UK CF Registry data, one using US CF Registry data), designed using the target trial emulation framework. Table 2 summarises the key components of the protocols for the target trial and the emulated trials.

**Table 2 T2:** Summary of key components of the protocol for the target trial and emulated trials

Protocol component	Target trial based on Clement *et al*^**16**^	Emulation of the target trial using UK CF registry data	Emulation of the target trial using US CF registry data
Eligibility criteria	Include: French individuals diagnosed with CF (sweat chloride >60 mmol/L or a genotype known to cause the disease), aged 6–21 years, with the ability to perform pulmonary function tests with FEV_1_%>40 and the ability to swallow tablets.Individuals were excluded if they had the following: Allergy to macrolide antibiotics Long-term (>3 months) with macrolides during the 12-month period before study entry Liver disease with liver function tests >2 times the laboratory upper limit History of portal hypertension Kidney disease with serum creatinine >150 µmol/L and/or creatinine clearance <50 mL/min Use of any of the following in the 3 months before study entry: DNase, inhaled tobramycin, inhaled steroids	Individuals will be considered for inclusion if they have a clinically confirmed diagnosis of CF (ie, are present in the UK CF Registry) and have an observation date within the recruitment periods defined in section 4.3.1, aged between 6 and 21 years, and obtained FEV_1_%>40 on their pulmonary function test (taken on the day of the annual review). It is assumed that all individuals have the ability to swallow tablets.Exclusion criteria are as follows: Intolerance to macrolide antibiotics recorded at any time during study period. Prescription of chronic oral or prophylactic oral macrolides (including azithromycin) recorded at time 0. Acute liver failure with >3×the upper laboratory limit, INR>2, or not responsive to vitamin K at time 0 Recorded cirrhosis with portal hypertension at time 0. Serum creatinine levels >150 µmol/L at time 0. Prescription of DNase, inhaled tobramycin or inhaled corticosteroids recorded at time 0. No follow-up visit for time 1.	Individuals will be considered for inclusion if they have a clinically confirmed diagnosis of CF (ie, are present in the US CF Registry) and have an observation or encounter date within the time periods defined in section 4.3.1, aged between 6 and 21 years, and obtained FEV_1_%>40 on their pulmonary function test (taken on the day of the encounter visit). It is assumed that all individuals have the ability to swallow tablets.Exclusion criteria are as follows: As in the UK Emulated Trial As in the UK Emulated Trial Non--related liver disease recorded at time 0. Laboratory results from liver tests are not available in the US registry. Recorded cirrhosis at time 0. Portal hypertension is not available in the US registry. As in the UK Emulated Trial As in the UK Emulated Trial As in the UK Emulated Trial
Treatment strategies	The active intervention was azithromycin supplied as 250 mg tablets and the comparator was placebo pills.Individuals weighing less than 40 kg took one tablet 3 days per week, and individuals weighing more than 40 kg took two tablets 3 days per week.	The active intervention is prescription of oral azithromycin and the comparator is no prescription of oral azithromycin.Further details are provided in the section titled "Treatment strategies".	
Assignment procedures	Individuals were randomised to treatment strategy. Randomisation was stratified according to centre and *Pseudomonas aeruginosa* infection status. The patients and all study investigators remained blinded to the treatment assignment until study completion.	In the emulated trials, individuals are not randomly assigned to the treatment strategy. This is accounted for in the analysis.	
Follow-up period	12 months	As in the target trial	
Outcome	Primary outcome: mean change in FEV_1_% between month 0 and month 12.Secondary outcomes included: evaluation of the number of pulmonary exacerbations, the use of antibiotics, modifications of microbiological analysis of sputum or throat cultures, changes in FVC, nutritional status with measurement of body mass index (BMI) and quality of life.	Primary outcome: absolute FEV_1_% at the end of follow-up.Secondary outcomes include: prescription of intravenous antibiotics, FVC, BMI z-score.Further details are provided in the section titled "Outcomes".	
Causal contrasts of interest	Intention to treat	Per-protocol	
Analysis plan	For continuous outcomes, mean differences between treatment groups were estimated using mixed models; for binary outcomes, logistic regression was used; for count outcomes, Poisson regression was used.	A direct acyclic graph is used to inform which variables need to be controlled for (see sectiontitled "covariates").Confounding by measured variables will be accounted for using inverse-probability-of-treatment weighting.Further details are provided in the section titled "Data analysis".	

CFcystic fibrosisFEV_1_forced expiratory volume in 1 sFVCforced vital capacity

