#### Definition of time 0 and the index visit

Time 0 is defined as the time at which individuals meet the eligibility criteria and ‘enter’ the emulated trial, analogous to the time of randomisation in the target trial. Time 1 is 12 months postbaseline, and the outcome of interest is forced expiratory volume in 1 s (FEV_1_%) at time 1.

For the emulated trials conducted within period p (p=1,2,3), we define an ‘index visit’ for each individual who meets the eligibility criteria during the recruitment period, such that the date of the index visit is time 0. Follow-up visits take place approximately 12 months after the index visit, and an eligibility criterion is that individuals are required to have a follow-up visit. Index visits and follow-up visits are defined differently in the UK and US emulated trials, due to differences in data collection between the two registries. Moreover, the visit we use for treatment, outcome and covariate data at time 0 and time 1 differs between the UK and US emulated trials; figure 1 summarises these differences.

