##### UK CF Registry Data

Using annual review data only

Within the period p, the index visit for a given individual is the first annual review visit at which they meet the eligibility criteria in the 2-year recruitment period. The follow-up visit is the date of the next annual review which is closest to 12 months after time 0, but falls within 9–15 months after time 0. The outcome is FEV_1_% measured on the day of the follow-up visit. Individuals are included in the treated group if they are recorded as being prescribed azithromycin at the follow-up visit because the information recorded on treatment use at the annual review refers to treatment use over the past year. Individuals not recorded as being prescribed azithromycin at the follow-up visit are included in the control group.

Using annual review data and prescription dates data

In the UK Registry, prescription dates data are available from 2016 onwards. Therefore, in period 3 (2016–2018), we can conduct a second analysis making use of the dates data for a more precise time 0. In the second analysis, the index and follow-up visits are defined as above for individuals in the control group. For treated individuals, the index visit is defined similarly; however, time 0 is defined as the first date post-index visit at which azithromycin is prescribed. The follow-up visit is defined as the next annual review visit which is closest to 12 months after time 0, but falls within 9–15 months after time 0.

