### Secondary outcomes

The secondary outcomes are prescription of intravenous antibiotics, per cent predicted FVC (FVC%) and BMI z-score. Analysis of the continuous outcomes (FVC% and BMI z-score) can be implemented as described above. Prescription of intravenous antibiotics will be treated as a time-to-event outcome (time to first prescription of intravenous antibiotics at home or in hospital) where censoring occurs at 365 days, or prior in the event of death or organ transplant. HRs will be estimated using Cox regression for the outcome models.

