### Missing data

The amount of missing data in each variable will be summarised in tables by treatment group. Where there are missing data in binary time-varying variables that are usually static for long time periods, we will use a simple imputation approach. For missing visits where the prior visit and subsequent visit are equal, we will assume the missing value is also equal and impute accordingly. This approach will be used for the following variables: pancreatic insufficiency, *P. aeruginosa*, *S. aureus*, NTM, CFRD, inhaled antibiotics, inhaled steroids, hypertonic saline and DNase. Missingness patterns in the remaining missing data will be explored. If there are missing outcomes that are missing at random conditional on C, then a complete case analysis is appropriate.^28^ If a complete case analysis is not appropriate, more complex missing data methods such as multiple imputation by chained equations^30^ may be considered.

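### Exclusion 1 (macrolide intolerance at any time) and exclusion 7 (no follow-up visit) decide eligibility from information after time 0, opening an uncorrected route to selection bias of unknown size and direction

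*Protocol article*

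**What the plan says.** In the Protocol article, the section on the definition of time 0 places time 0 at the moment eligibility is met and describes it as "analogous to the time of randomisation in the target trial". In Table 2 (Study design), UK exclusions 2 to 6 are all read at time 0. Two exclusions are not:

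- Exclusion 1 is "Intolerance to macrolide antibiotics recorded at any time during study period". The target-trial column lists "Allergy to macrolide antibiotics" among its entry exclusions.
- Exclusion 7 is "No follow-up visit for time 1". The time 0 section confirms that "an eligibility criterion is that individuals are required to have a follow-up visit".

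The US column adopts both by reference to the UK column. The UK follow-up visit is the annual review "closest to 12 months after time 0, but falls within 9–15 months after time 0". In the US it is the stable encounter visit in the same window after the index visit.

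Under Secondary outcomes, time to first intravenous antibiotics is analysed as a time-to-event outcome, "where censoring occurs at 365 days, or prior in the event of death or organ transplant". The Limitations section covers dose, adherence, the liver criterion, visit spacing, unmeasured confounding and population differences. It mentions neither exclusion 1 nor exclusion 7 as a source of selection.

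**The concern.** In a randomised trial nobody can be declared ineligible because of something that happens after allocation. An emulation keeps that protection only if eligibility is settled with what is known at time 0.

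Intolerance is often discovered by taking the drug. Counting later records can therefore remove people who started azithromycin and reacted to it, while equally prone people who never took it stay in the control group. The term study period is not defined in the criterion. If it means the three-year time period, someone indexed at its start has the outcome after one year, and a record in the remaining two years (3 − 1) would still exclude them.

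Requiring a later visit keeps only those who return. In the US the visit must also be stable, and the US registry section says that hospital and home intravenous visits may reflect respiratory deterioration, so the requirement may be related to prognosis.

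The study's purpose is to judge agreement with a published trial. Selection of this kind does not shrink with the larger samples expected, so it could produce false agreement or false disagreement.

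**Working it through.** The plan gives no rate of intolerance, missed follow-up or early death, so there is no figure to reproduce. The steps below set out the mechanism and illustrate its size. Every rate is an assumption.

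**Set-up.** Simulation of 2,000,000 people with a true treatment effect of 0. Baseline FEV1% contributes 15 points per SD and is in the covariate set C. An unmeasured prognostic factor U contributes 7 points per SD. Residual SD is 5. Estimation is AIPTW with a logistic propensity model and a linear outcome model, as under Main analysis. With no selection the estimate is −0.004, which is simulation error. Positive values favour azithromycin.

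**Exclusion 1.** Let π be the share who would prove intolerant if exposed, and d the amount by which their 12-month FEV1% is worse. If prone people are removed from the treated group only, the treated mean is μ and the control mean is μ − πd, so bias = π × d.

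| π | d | π × d | simulated |
|---|---|---|---|
| 0.02 | 0 | 0 | −0.003 |
| 0.05 | 0 | 0 | 0.000 |
| 0.10 | 0 | 0 | −0.004 |
| 0.02 | 5 | 0.10 | 0.097 |
| 0.05 | 5 | 0.25 | 0.245 |
| 0.10 | 5 | 0.50 | 0.487 |
| 0.02 | 10 | 0.20 | 0.198 |
| 0.05 | 10 | 0.50 | 0.496 |
| 0.10 | 10 | 1.00 | 1.001 |

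The bias exists only if intolerant people differ in prognosis, and its sign is the sign of d.

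**Exclusion 7.** Attendance is logistic in arm and in U.

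| Attendance, treated v control | Slope on U, treated / control | Bias |
|---|---|---|
| 88.1% v 88.1% | 0 / 0 | 0.005 |
| 81.7% v 88.1% | 0 / 0 | −0.004 |
| 87.1% v 87.1% | 0.5 / 0.5 | 0.000 |
| 80.6% v 87.1% | 0.5 / 0.5 | 0.201 |
| 87.1% v 88.1% | 0.5 / 0 | 0.431 |
| 84.5% v 87.1% | 1.0 / 0.5 | 0.520 |

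There is no bias when attendance depends on arm alone, or on prognosis equally in both arms with equal attendance. Bias appears when attendance depends on both treatment and prognosis beyond C. In these scenarios treated people with poor prognosis are the ones lost; exchanging the roles of the arms reverses the sign.

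**Exclusion 7 against the censoring rule.** The window opens at 9 months, about 365 × 9/12 = 274 days. Anyone who dies before then cannot have a follow-up visit and is already excluded, so censoring at death never applies to them. Between about day 274 and day 365, a death is retained only if the visit came first. The conflict with the Secondary outcomes section is therefore real but partial.

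**The case against.** The strongest reply is that the emulated contrast is per-protocol. Someone who stops for intolerance has left the strategy of taking azithromycin for 12 months, so the absence of a counterpart in an intention-to-treat result is not itself an error. That stands. It does not rescue exclusion 1, because the estimand section takes its expectations over people meeting the target trial's criteria, and that includes people who later prove intolerant. Stopping is a deviation after baseline, not ineligibility.

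A second reply is that observation weights built on treatment and C rest on much the same missing-at-random assumption as the planned complete-case analysis. Largely true: they do not remove dependence on unmeasured prognosis. They do restore the intended population when attendance depends on measured factors, and they make the selection visible by arm.

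A third is practical, and it stands. In the UK annual-review analysis the arm is read at the follow-up visit, so a person without that visit has no known treatment, and outcome-observation weights alone cannot work there.

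A reader might infer that both rules always favour azithromycin. The documents do not support this: nothing in them says that intolerant people or non-attenders have worse lung function, and the tables give zero bias without such a link. A reader might also infer that every transplanted person is lost. Exclusion 7 removes only those without a visit; a transplanted person who attends remains, and the censoring rule can still apply to them.

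**Conclusion.** The point holds for exclusions 1 and 7. Both condition eligibility on events after time 0, against the plan's own definition of time 0, and nothing planned corrects for it. Exclusion 1 is the clearer fault, since it departs from how the plan reads exclusions 2 to 6 and from the target trial's entry criterion. Exclusion 7 is conditional: if attendance depends only on treatment and C, AIPTW stays unbiased for the population that returns, although that population is narrower than the one in the estimand.

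The size is not determined by the documents. The ranges of 0 to 1.0 points (exclusion 1) and 0 to 0.5 points (exclusion 7) rest entirely on the assumed intolerance shares, prognostic gaps and attendance patterns.

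A reader might infer a third instance from the imputation rule under Missing data: "For missing visits where the prior visit and subsequent visit are equal, we will assume the missing value is also equal and impute accordingly". It should not be counted as an error. The filled value always equals the prior-visit value, and the later visit decides only whether the gap is filled. In simulation the rule gave −0.004 to −0.192 points across 5% to 40% missingness, while carrying the prior value forward for everyone gave −0.017 to −0.195, so using the prior visit alone brought no gain.

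**What to change.** 1. **Exclusion 1, both registries.** Change to macrolide intolerance recorded at or before time 0. Cost: a few words.
2. **Exclusion 7, US.** Treatment is known at the index visit, so remove the visit requirement from eligibility. Treat an absent stable visit at 9–15 months as a missing outcome, with inverse-probability-of-observation weights in the AIPTW. Analyse the date-based intravenous-antibiotic outcome in all eligible people, so that censoring at death or transplant can operate. Cost: one extra weight model and no new data.
3. **Exclusion 7, UK annual-review analysis.** Keep the requirement, but describe it as an analysis-set restriction and not as eligibility. Weight attenders by the inverse of their probability of attendance given baseline C. State in the Limitations section that selection depending on treatment or on unmeasured prognosis remains. Cost: one weight model and a short paragraph.

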### Setting

#### Time periods

The target trial was conducted from 2001 to 2003, with results published in 2006. Within the data collection period for the target trial, results from other azithromycin RCTs were published,^22^,^24^ after which there was uptake of this treatment in routine clinical practice. We plan to emulate the trial using data from three time periods of 3 years’ duration: 2003–2005, 2007–2009, 2016–2018. Period 1 is close to the timing of the target trial while allowing time for the treatment to have come into use. Periods 2 and 3 were chosen based on features of the data, and ending the time frame in 2018 means that we only use data from the time before CFTR modulators became widespread in clinical practice.

Table 3 provides further details and justification about the three time periods. For each 3-year time period, the first 2 years are used as the ‘recruitment period’, defined as the period during which individuals are considered for inclusion in the emulated trial. The target trial recruited participants over 2 years. Individuals are included in the emulated trial data if they meet the inclusion and exclusion criteria in at least one of their visits during the recruitment period.

**Table 3 T3:** Description of the time periods considered in the UK and US registry data

Time period	Justification for time period	UK data	US data
2003–2005	Closest time period to the target trial, allowing a couple of years for use of azithromycin to uptake in clinical practice.This will only be conducted using the UK data as the US registry did not collect data on azithromycin use during this time.	✓	×
2007–2009	The US registry started collecting data on azithromycin in 2006 and a 1-year wash-out period is required to select individuals who were not taking azithromycin prior to study entry. Therefore, this time period is as close to the time period used in the target trial as is possible for the US registry.	✓	✓
2016–2018	The UK registry started collecting data on treatment prescription dates in 2016. Therefore, this time period is a more recent period that predates widespread use of CFTR modulators but also allows use of treatment date data.	✓	✓

CFTRcystic fibrosis transmembrane conductance regulator

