##### US CF Registry Data

Within the period p, the index visit is defined as the first stable encounter visit at which an individual meets the eligibility criteria in the 2-year recruitment period. The follow-up visit is defined as the date of the stable encounter visit that is closest to 12 months after the index visit, but which falls within 9–15 months after the index visit. Individuals are included in the treatment group if they are recorded as being prescribed treatment at the index visit, as this is often assumed to be the treatment start date. Once an individual starts treatment, we assume they remain on treatment until the follow-up visit. Individuals are included in the control group if they are recorded as not being prescribed azithromycin at the index visit. Controls who are recorded as starting treatment at an encounter visit between the index visit and the follow-up visit are censored at the date of that encounter visit. For the US emulated trials, we also define the prior visit to be the most recent stable encounter visit prior to the index visit.

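### US emulations: the macrolide exclusion and the treatment assignment are read at the same visit, so as worded no treated person is eligible

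*Protocol article*

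**What the plan says.** Table 2 (protocol article, Study design) lists the exclusions by emulation. The second UK item is "Prescription of chronic oral or prophylactic oral macrolides (including azithromycin) recorded at time 0". The US list begins "Exclusion criteria are as follows: As in the UK Emulated Trial As in the UK Emulated Trial Non--related liver disease recorded at time 0", so its second item is the UK macrolide rule with the UK timing.

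The section defining time 0 and the index visit states "Time 0 is defined as the time at which individuals meet the eligibility criteria" and fixes the index visit "such that the date of the index visit is time 0". For the US, "the index visit is defined as the first stable encounter visit at which an individual meets the eligibility criteria in the 2-year recruitment period". Assignment is made at that visit: "Individuals are included in the treatment group if they are recorded as being prescribed treatment at the index visit". People without azithromycin at the index visit are controls. Controls who start before the follow-up visit are censored at the encounter where the start is recorded.

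Table 3 explains the 2007 start of the first US period by saying that "a 1-year wash-out period is required to select individuals who were not taking azithromycin prior to study entry".

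The UK works differently. In the annual-review analysis, treatment is read at the follow-up review. In the prescription-date analysis for 2016–2018, the index visit is still an annual review at which eligibility is met, but for treated people "time 0 is defined as the first date post-index visit at which azithromycin is prescribed".

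**The concern.** An exclusion meant to select new users has to look backwards from the point where treatment is assigned. In the US rules as worded, the exclusion and the assignment use the same variable at the same visit, so being treated implies being ineligible.

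Two things are at stake. First, the US rules cannot be programmed as written, so an analyst must change them. The change could be a check at one earlier visit, at all visits in a year, or at some other window, and each choice gives a different cohort. In a study whose purpose is to see whether a trial can be replicated, that choice should be fixed before the data are seen. Second, the rule does not remove prior users who are off azithromycin at the index visit. They may enter the comparator arm even though Table 3 says the wash-out exists to keep prior users out.

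**Working it through.** The plan gives no figure to reproduce here, so the check is logical.

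**Inputs**
- E: excluded if a chronic or prophylactic oral macrolide, azithromycin included, is recorded at time 0 (Table 2, exclusion 2, adopted by the US column).
- Time 0 = date of the index visit (definition of time 0).
- Treated (A = 1): azithromycin recorded at the index visit; control (A = 0): not recorded there (US CF Registry Data).
- Later starters stay in the control group and are censored (same section).

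**US: the four possible histories under the written rules**

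| Azithromycin at prior visit | Azithromycin at index visit | Exclusion 2 | Result |
|---|---|---|---|
| no | no | not met | control |
| no | yes | met | excluded |
| yes | no | not met | control |
| yes | yes | met | excluded |

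No row yields an eligible treated person. The treated set lies inside the excluded set, so treated and eligible together are the empty set. Later starters cannot refill the arm. The third row is the second fault: a person with recorded use before entry becomes a control.

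**Consequence for the estimator.** With no one treated, P(A = 1 | C) = 0 throughout the cohort. The positivity assumption in the Main analysis section fails. The treated mean in equation 5 divides by P(A = 1 | C), so it cannot be computed.

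**US: the same histories if exclusion 2 looked back before the index visit**

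| Prior | Index | Result |
|---|---|---|
| no | no | control |
| no | yes | treated (new starter) |
| yes | no | excluded |
| yes | yes | excluded |

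This is the new-user comparison that Table 3 describes. Re-timing the one rule repairs both faults.

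**UK annual-review analysis.** Exclusion 2 is read at the index review and treatment at the follow-up review about a year later. These are different visits, so there is no clash.

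**UK prescription-date analysis.** Eligibility is met at the index review and the first prescription comes later. With exclusion 2 read at the index review, treated people remain. They are lost only if the time 0 of Table 2 is taken to be the prescription date.

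**The case against.** The strongest reply is that the intent is plain. Table 3 speaks of people not taking azithromycin before entry, the US section defines a prior visit that the UK does not need, and nobody would run a US emulation with no treated patients. The article also says that the visit supplying time-0 data differs between the registries and refers to Figure 1, which was not visible to this review and may place medication history at the prior visit. Much of this stands: it makes a truly empty arm unlikely in practice. It does not reconcile the stated rules. The prior visit is not tied to exclusion 2 anywhere in the text. It is only the most recent stable encounter, which need not be a year earlier, so it would not by itself deliver a 1-year wash-out. Nor is this an omission explained by a condensed article, because rules that are stated conflict with one another.

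A reader might infer that the UK prescription-date analysis is equally empty, because time 0 for its treated group is itself a prescription date. The text does not support that. The index visit for treated people is defined as for everyone else, as the first annual review at which the criteria are met, so eligibility is settled before the prescription. What remains is one label, time 0, used for two dates.

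A reader might also infer that no wash-out is implemented anywhere. That is wrong for the UK, where the annual-review treatment record covers the past year, so exclusion 2 at the index review already looks back about a year.

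**Conclusion.** The contradiction is real and confined to the US emulations. As worded, all treated people are excluded in both US periods. This follows from the definitions alone, with no assumption about data. The same wording admits some prior azithromycin users as controls; the documents give no count from which to size that group.

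This is an error in a written rule, not evidence that the US study will actually have no treated arm. The realistic consequence is an unplanned choice of look-back window. That assessment rests on the visible text; Figure 1 could show the intended timing, but Table 2 and the US section would still need to be reconciled with it. The UK annual-review analysis is sound on this point, and the UK prescription-date analysis needs a clarification only.

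**What to change.** Give the US column of Table 2 its own exclusion 2: no chronic or prophylactic oral macrolide, azithromycin included, on any encounter record in the 12 months before the index visit, with the index visit itself not counted. This puts the Table 3 wash-out into the eligibility rules. Check that Figure 1 agrees.

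State two consequences beside the rule. It may be stricter than the target trial, which excluded only more than 3 months of macrolide use in the prior 12 months. It will also lose some people who lack a 12-month look-back; the documents do not allow that number to be estimated.

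For the UK prescription-date analysis, add that exclusion 2 is assessed at the index review and not at the later prescription date called time 0 for treated people. No dated 12-month look-back is needed. It would be partly unavailable anyway, because UK prescription dates start in 2016, the first year of that recruitment period. Leave the UK annual-review rule as it is.

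The cost is a few lines of protocol text, one change to the US cohort code and the lost US patients noted above.
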